## ABBREVIATIONS AND DEFINITIONS

MIC: Minimum inhibitory concentration

*S. aureus*: *Staphylococcus aureus*

IV: intravenous;

HU: University Hospital

HUVM: University Hospital Virgen Macarena

HUVV: University Hospital Virgen de Valme

Community presentation: Infection occurring in a patient who was not hospitalized during the previous week, or starts within 72 hours of a hospital admission (this definition includes community infections and non-nosocomial healthcare-related infections).

Adverse Event: Any adverse or unfavorable event that appears in a study participant, including any sign, symptom or disease, whether or not considered to be related to the drug administered.

### **2. Title of the study.**

“Identificación y validación de fenotipos clínicos en bacteriemias por *Staphylococcus aureus* y su asociación con la mortalidad y desarrollo de bacteriemia complicada (FEN-AUREUS study)” (Identification and validation of clinical phenotypes in *Staphylococcus aureus* bacteremia and their association with development of complicated bacteremia and mortality).

### 3. Protocol code (according to official coding guidelines).

FIS-FENAUREUS-2022-01

## 6. Research Ethics Committee (REC) evaluation

Requires the favorable opinion of the Andalusian Biomedical Research Ethics Coordinating Committee (in process).

## 7. Primary objective.

To determine retrospectively whether different clinical phenotypes exist among patients (adults and children) who develop *Staphylococcus aureus* bacteremia.

Secondary objectives:

### Secondary objectives:

- 1 To evaluate the reproducibility of these clinical phenotypes and their correlation with mortality (30 days and 6 months)
- 2 To derive and validate a simplified probabilistic model of phenotype assignment.
- 3 External validation of the simplified probabilistic model of clinical phenotype assignment in a prospective cohort, and determination of associations with mortality and the development of complicated bacteremia within 6 months.
- 4 To apply microbiological (clonality testing, genome sequencing), biochemical and immunological techniques to elucidate the pathophysiological and genetic mechanisms underlying the phenotypes.

## 8. Design.

This is an entirely observational study.

Primary Objective and Secondary Objectives 1 and 2: The ISAC cohort will be analyzed. This cohort is the result of an international study (11 hospitals in 5 countries) on bacteremia caused by *S.aureus* (2,590 cases collected) in which the University Hospital Virgen Macarena participated. The other participating centers have granted authorization to carry out the analysis for the FEN-FENAUREUS project.

Secondary Objectives 3 and 4: This will be a multicenter prospective cohort study. Each patient who develops *S. aureus* bacteremia will be assigned a phenotype and will be followed for 6 months to evaluate differences in mortality and development of complicated bacteremia according to phenotype.

For Secondary Objective 5: This study of genetic (microorganism and the patient), immunological, biochemical and microbiological variables will be performed on representative patients, selected from the prospective cohort (two centers HUVM and HUVV), with the different phenotypes obtained.

Inclusion criteria: adults and children with clinically significant *S. aureus* bacteremia (i.e., associated with at least 2 of the classic criteria for systemic inflammatory response: fever, tachycardia, tachypnea, decreased level of consciousness, hypotension, leukocytosis/leukopenia, or organ failure).

For the study of genetic, immunological, biochemical and microbiological variables in representative patients, a predefined number of patients with each of the phenotypes assigned by the probabilistic model will be randomly selected from the prospective cohort (at the HUV and HUVV).

Exclusion criteria: Non-clinically significant bacteremia; lack of follow-up blood cultures at 48-72 hours; patients who died in the first 48 hours; subsequent episodes in the same patient.

## **9. Disease or disorder under study.**

Clinically significant *S. aureus* bacteremia

## **10. Details of the drugs under study.**

The type of antibiotic treatment administered will be only one of the explanatory variables that will be collected (indicated below) and recorded in order to achieve the proposed objectives set out above. Therefore this study IS NOT CONSIDERED AN OBSERVATIONAL STUDY WITH MEDICINES, AS IT DOES NOT FALL UNDER ANY OF THE SUPPOSITIONS GIVEN IN ARTICLE 2 OF ROYAL DECREE 957/2020, OF NOVEMBER 3, REGULATING OBSERVATIONAL STUDIES WITH MEDICINES FOR HUMAN USE, and in no case does it alter the prescribing practice of the physician, or the dispensing practice of the pharmacist. The prescription of medication will follow the usual pathway.

## **11. Study population and total number of subjects**

For the retrospective study (objectives 1-3) based on the ISAC database, we estimate that we will be able to analyze at least 1,800 cases of SAB that meet the inclusion criteria. Likewise, for objective 4, we estimate that 1,000 cases will be prospectively included from the 14 participating centers during the 34 months of follow-up. For objective 5, given that we estimate that 3 or 4 phenotypes will be identified, 100 patients/ isolates will allow us to include 25-33 per phenotype, which will allow a reasonable number of cases for comparison of microbiological, genetic, endothelial and immunological parameters.

## **12. Schedule (quarterly periods indicated)**

- January to May 2022: Retrospective cohort analysis of ISAC.

- March to May 2022: Registration in the REec (Spanish Registry of Clinical Trials) (if considered necessary); preparation of electronic datasheets; submission of documentation to the Andalusian Biomedical Research Ethics Coordinating Committee; sending of documentation to participating centers; piloting of the data collection sheet.
- June 2022 to June 2024: Inclusion of patients in prospective cohort, sample collection; data collection and recording in electronic datasheet.
- September 2022 to June 2024: Study of genetic (microorganism and patient), immunological, biochemical and microbiological variables.
- June 2022 to June 2024: Data monitoring; database review for missing/inconsistent data. Closure of database.
- Third quarter 2024: Data analysis.
- Fourth quarter 2024: Publication of results.

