## METHODS:

### Design and justification.

This is an entirely observational study.

For the Primary Objective and Secondary Objectives 1 and 2: the ISAC cohort will be analyzed. This cohort is the result of an international study (11 hospitals in 5 countries) on bacteremia caused by *S. aureus* in which the Hospital Virgen Macarena participated (2,590 cases have been collected, and it is estimated that at least 1,800 meet the criteria for inclusion). Authorization to perform the analysis for the FEN-FENAUREUS project has been obtained from the rest of the participating centers.

For Secondary Objectives 3 and 4 a multicenter prospective cohort study will be performed. All patients who develop *S. aureus* bacteremia will be assigned a phenotype and followed for 6 months to evaluate differences in mortality and development of complicated bacteremia between phenotypes.

For Secondary Objective 5 a study of genetic (microorganism and patient), immunological, biochemical and microbiological variables will be performed in representative patients with different phenotypes; these patients will be selected from the prospective cohort at two centers (HUVV and HUVV).

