### 4. Operational definitions of outcome, exposure and other variables.

- Outcome variables:
  - Primary outcome variable: all-cause mortality at day 30;

Secondary outcome variable: all-cause mortality at month 6 (measured as time-to-death, prospective cohort only). Persistent bacteremia (positive blood culture 2-3 days after initiation of appropriate targeted therapy). Complicated bacteremia (considered as presence of endocarditis, secondary foci, recurrence within 6 months). Hospital stay.

- 
- 

Explanatory: age, sex, service, type of acquisition (community-acquired, healthcare-related, nosocomial [Friedman criteria]; types of relationship with previous care), underlying diseases (diabetes, chronic lung disease, chronic renal insufficiency, chronic liver disease, immunosuppressive disorders, cancer, other), severity of underlying disease (Charlson index, McCabe classification), Barthel index, neutropenia, parenteral drug use, immunosuppressive treatment, recent invasive procedures (dialysis, catheter and vascular type, urinary catheter, mechanical ventilation, endoscopy, vascular procedures, surgery, percutaneous puncture), antibiotic therapy in the previous month, antibiotic susceptibility of *S. aureus*, Pitt and SOFA score on day 0 (blood cultures performed), sepsis or septic shock (Singer et al. JAMA 2016 for adults and Dellinger et al, Intensive Care Medicine 2013//Mathias et al, Curr Opin Pediatr 2016 for pediatric patients), acute kidney injury, empiric and targeted antibiotic therapy (drug, dose, route, day of onset and termination, reason for termination), source of bacteremia (clinical and microbiological criteria), management of source of infection (removal of catheter or other device, drainage), supportive care, echocardiographic data, if performed (transthoracic/transesophageal), CBC and basic blood chemistry at 0.

Exposure variables: Type of phenotype

- 

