## 5. Expected sample size and basis for determination.

For the retrospective study (objectives 1-3) based on the ISAC database: we estimate that we will be able to analyze at least 1,800 cases of SAB that meet the inclusion criteria. For objective 4: we estimate prospective inclusion of 1000 cases from the 14 participating centers during 34 months of follow-up.

For objective 5: we estimate that 3 or 4 phenotypes will be identified, and therefore that 100 patients/isolate will be sufficient to provide 25-33 patients per phenotype, which will allow a reasonable number of cases for comparison of microbiological, genetic, endothelial and immunological parameters.

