#### CONSIDERATIONS IN PEDIATRIC PATIENTS

We estimate that 340 cases will be prospectively included from 17 participating centers during the 34-month follow-up.

Microbiology and immunology testing procedures will be similar to those in the adult cohort, adjusting blood collection volume to the maximum allowed for age and weight in pediatric patients.

Recent studies have suggested the involvement of an altered IL17 immune response in the context of invasive infections (CID 2019, PMID: 30165412), although it is most commonly described in the context of *S. aureus* of the skin and mucous membranes. Consequently, we propose to determine circulating IL-17A and Th17 (CD4+CXCR3-CCR6 +CCR4+ CD161+) levels at the time of blood culture sampling in the prospective cohort (Laboratorio 205, “Errores Innatos de Inmunidad”, Ibis; Laboratory 205, “Inborn Errors of Immunity”, Ibis).

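### Inclusion and database closure both end in June 2024, so about a quarter of the prospective cohort would lack complete 6-month follow-up; the 34-month accrual period also does not match the dated 25-month window

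*Combined protocol and SAP*

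**What the plan says.** The protocol summary, section 12 (Schedule), has these rows for the prospective cohort:

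- Inclusion: "June 2022 to June 2024: Inclusion of patients in prospective cohort, sample collection; data collection and recording in electronic datasheet".
- Cleaning and closure, on the same dates: "June 2022 to June 2024: Data monitoring; database review for missing/inconsistent data. Closure of database".
- Analysis: "Third quarter 2024: Data analysis".

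The Work Plan table repeats these dates, with analysis in July to September 2024 and publication in October to December 2024.

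On follow-up, section 8 (Design) says that each patient "will be followed for 6 months to evaluate differences in mortality and development of complicated bacteremia according to phenotype", and the Methods section on design says the same. Methods section 4 (Operational definitions) lists as a secondary outcome "all-cause mortality at month 6 (measured as time-to-death, prospective cohort only"), and counts recurrence within 6 months as part of complicated bacteremia. Methods section 8 (Data analysis) compares mortality rates at 30 days and six months, and complicated bacteremia, between phenotypes, and leaves the model open between Cox and logistic regression.

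On numbers, Methods section 5 says "we estimate prospective inclusion of 1000 cases from the 14 participating centers during 34 months of follow-up", and section 11 of the summary agrees. The pediatric section adds: "We estimate that 340 cases will be prospectively included from 17 participating centers during the 34-month follow-up".

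**The concern.** Two sets of statements do not fit together.

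First, a patient included in the last six months of the window cannot complete 6 months of follow-up before a closure in the final month of inclusion. No row of the schedule provides a follow-up period after the last inclusion. The dissemination section ties first publication to the end of inclusion and closure of the database, not to completed follow-up. The data analysis section names no censoring rule and no 6-month analysis set. If late patients enter a rate or a logistic model, the plan does not say whether they count as event-free or are left out. Secondary objective 3 (numbered objective 4 in the sample-size and analysis sections) rests on these 6-month outcomes.

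Second, the expected case numbers are tied to a period that the dated schedule does not contain, so a reader cannot tell how many cases the plan expects by its own closing date.

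**Working it through.** **Inputs.** Inclusion June 2022 to June 2024, closure in a row ending June 2024, and analysis in the third quarter of 2024 (section 12 and Work Plan). Follow-up of 6 months per patient (section 8; Methods, design). 1,000 cases in 34 months (section 11; Methods 5). 340 pediatric cases in 34 months (pediatric section). The documents give no monthly accrual rate and no day of closure, so uniform accrual and closure at the end of June 2024 are assumptions.

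**Length of the window.** June 2022 to June 2024 inclusive is 7 + 12 + 6 = 25 calendar months, or 24 if counted from June to June.

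**Share without complete 6-month follow-up.** These are the patients included January to June 2024.
- 6/25 = 24%; with a 24-month window, 6/24 = 25%.
- If all 1,000 cases were included in this window, that is 240 to 250 patients.
- If closure slipped to the end of September 2024, the end of the analysis quarter, the share would be 3/25 = 12%.
- The share reaches zero only with closure at the end of December 2024.

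**Share without full 30-day follow-up.** The last month of inclusion: 1/25 = 4%.

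**Effect if late patients were counted as event-free.** This is an illustration; the plan does not say that they would be. The proportional understatement of a 6-month event rate is 24% times the average fraction of events that falls after closure in these patients. If events are spread evenly over the 6 months, that fraction is one half: 0.24 × 0.5 = 12%. The range runs from near 0% (all events at onset) to 24% (all events at month 6).

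**Can the stated 34 months be reproduced?**
- Inclusion window: 25 months (or 24).
- Inclusion plus 6 months of follow-up: 25 + 6 = 31 months.
- 34 months read as inclusion plus follow-up: 34 − 6 = 28 months of inclusion, still not 25.
- 34 months of inclusion from June 2022 would end in March 2025, after the planned publication quarter.
- March 2022 to December 2024 is 10 + 12 + 12 = 34 months, but that span includes set-up, analysis and publication.

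None of these makes 34 months the inclusion period.

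**Expected numbers, for illustration only.** If 34 months is taken as the accrual period and accrual is uniform:
- 1,000/34 = 29.4 per month; × 25 = about 735 cases; × 19 = about 559 of them included by the end of December 2023.
- 340/34 = 10 per month; × 25 = about 250 pediatric cases.
- To reach 1,000 in 25 months takes 1,000/25 = 40 per month, and 40/29.4 = 1.36, a pace 36% faster.

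**The case against.** **Time-to-death is already planned.** Month-6 mortality is defined as time-to-death and Cox regression is allowed. Late patients can be censored at closure and their deaths before it still count. This stands. A reader might infer that a quarter of the cohort has no usable 6-month outcome; the documents do not support that. What these patients lack is complete follow-up. The problem remains for the comparison of six-month rates, for any logistic model, and for recurrence within 6 months, which is nowhere described as a time-to-event outcome.

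**The dates are coarse.** The schedule is headed as quarterly, the inclusion row also covers data collection, and closure has no date of its own. Inclusion could therefore be read as stopping about December 2023, with the remaining months used for follow-up. That reading closes the follow-up gap, but it cuts inclusion to about 19 months and moves it further from 34. No reading of the dates resolves both conflicts.

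**The 1,000 is an estimate.** There is no power calculation, and 34 months may simply be a project duration carried over. A reader might infer that the cohort would fall to about 735. That does not follow: the monthly rate is inferred, and the error may lie in the period and not in the number. Table S9 of the appendix reports 283 + 573 + 329 = 1,185 FEN-AUREUS patients, above 1,000. It gives no inclusion dates, so it neither reconciles the schedule nor shows that 6-month follow-up was complete. It is also unstated whether the 340 pediatric cases are part of the 1,000, so the 1,000 cannot be read as adults only.

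**Conclusion.** The concern holds as an inconsistency in the plan, limited to secondary objective 3. With the dates as written, about 24% of the prospective cohort (25% with a 24-month window) would lack complete 6-month follow-up at closure, and about 4% would lack a full 30 days. Both figures assume uniform accrual and closure at the end of June 2024. Six-month rates, logistic models and complicated bacteremia including recurrence are exposed; time-to-death with censoring is not. Separately, the 34 months attached to the 1,000 and the 340 cases do not match the 25-month window.

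The primary objective is not affected, because it uses the ISAC cohort, and day-30 mortality is little affected. Nor do the documents show that reported results are biased: the survival results that the appendix gives for FEN-AUREUS concern 30-day mortality only.

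**What to change.** Choose one of two changes to section 12, the Work Plan and Methods section 8:

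- **(a)** Move database closure to no earlier than the end of December 2024 and analyse after that. All patients included through June 2024 then complete 6 months, and simple proportions raise no closure problem. Cost: about 6 months' delay.
- **(b)** Keep the dates. Restrict rate and logistic comparisons of 6-month outcomes to patients included by 31 December 2023, and 30-day comparisons to those included by 31 May 2024. Analyse the full cohort by time-to-event methods with administrative censoring at closure. Cost: a smaller 6-month set, 19 of 25 inclusion months, or 76% of the cohort under uniform accrual.

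If inclusion was meant to stop before June 2024, give it a row and an end date of its own.

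In either case, reconcile the 34 months with the dated window in section 11, Methods section 5 and the pediatric section. Either correct the period, or restate the expected numbers with the accrual assumption shown. The figures of about 735 and 250 illustrate the size of the mismatch and should not be entered as new targets. State as well whether the 340 pediatric cases are included in the 1,000. This part costs wording only.

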### 13. Source of funding.

There is no financial compensation for patients or investigators, nor are there any undeclared sources of funding that could lead to conflicts of interest in the research results.

### WORK PLAN (TASKS, MILESTONES AND STUDY TIMELINE.

| Month-Year           | Task                                                                                                                                                                                                                                      | Responsible                        |
|-----------------------------|--------------------------------------------------------------------------------------------------------------------------------------------------------------------------------------------------------------------------------------------------|-------------------------------------------|
| January 2022-May 2022       | Retrospective cohort analysis of ISAC                                                                                                                                                                                                            | Principal investigators                   |
| March 2022-May 2022         | Registration in REec; preparation of electronic datasheet; submission of documentation to the Andalusian Biomedical Research Ethics Coordinating Committee; sending of documentation to participating centers; piloting of data collection sheet | Principal investigators                   |
| June 2022-June 2024         | Inclusion of patients in prospective cohort, sample collection; data collection and recording in electronic datasheet                                                                                                                            | Principal investigators and collaborators |
| September 2022 to June 2024 | Study of genetic (microorganism and patient), immunological, biochemical and microbiological variables.                                                                                                                                          |                                           |
| June 2022 to June 2024      | Data monitoring; database review for missing/inconsistent data.                                                                                                                                                                                  | Principal investigators and               |

|                            |                        |                                           |
|----------------------------|------------------------|-------------------------------------------|
|                            | Closure of database.   | collaborators                             |
| July 2024- September 2024  | Analysis of results    | Principal investigators and collaborators |
| October 2024-December 2024 | Publication of results | Principal investigators and collaborators |

## GENERAL AND SPECIFIC OBJECTIVES: BASES

### Primary Objective

To determine retrospectively whether patients (adults and children) who developed bacteremia caused by *Staphylococcus aureus* had different phenotypes.

### Secondary Objectives

- 1 To evaluate the reproducibility of the clinical phenotypes and their correlation with mortality (30 days and 6 months).
- 2 To derive and validate a simplified probabilistic model of clinical phenotype assignment.
- 3 External validation of the simplified probabilistic model of clinical phenotype assignment in a prospective cohort and determination of associations with mortality and the development of complicated bacteremia within 6 months.
- 4 To apply microbiological (clonality testing, genome sequencing), biochemical and immunological techniques to elucidate the pathophysiological and genetic mechanisms underlying the phenotypes.

